## Study design

This pragmatic multi-methods study comprises three discrete but related components: concurrent retrospective quantitative data collection for Components 1 and 2, and prospective qualitative data collection for Component 3. The approach to quantitative and qualitative data collection enables a comprehensive examination of the model’s effectiveness and real-world application. Given the multi-methods design, integration of quantitative and qualitative data through triangulation will not be undertaken. The design is underpinned by the integrated Practical, Robust, Implementation and Sustainability Model (PRISM) and Reach, Effectiveness, Adoption, Implementation and Maintenance (RE-AIM) framework [45]. PRISM will support the identification and description of contextual factors impacting RE-AIM outcomes [45]. This study has been reviewed and approved by the Metro North Human Research Ethics Committee (HREC) B (ECOO168), approval number 102,923. Data storage, retention and disposal will be conducted in accordance with the National Health and Medical Research Council (NHMRC) guidelines [46].

Three components are planned to address the following research questions:

*Component 1*

To what extent (if any) do patient characteristics (such as age, sex, and diagnostic classification^6^) and outcomes differ between OPEN AOS care and standard care (i.e. ambulance attendance with transport to ED care)?Specifically:

4.Primary Outcome: Time to be seen by treating clinician, defined as the amount of time in minutes from the initial contact with QAS to the time seen by either (i) the OPEN AOS clinician (intervention group) or (ii) the ED medical officer (control group).5.Secondary Outcomes:6.Length of care episode, defined as the amount of time in hours from initial contact with QAS to discharge of care.7.Ambulance transport to ED care: defined as the proportion of OPEN AOS patients requiring transport to ED for definitive care.8.ED re-presentation for any cause within 48 h and 28 days of discharge.9.Death within 48 h of discharge.10.Clinical incident^7^ [47] data, defined as clinical incidents that are reported by MNHHS staff that occur within 48 h of discharge.

*Component 2*

Compared to standard care, what is the incremental cost (saving) per person of the OPEN AOS model? 

*Component 3*

How do contextual factors influence implementation and potential future scale and spread of the OPEN AOS model?

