### Data collection and linkage

Patients living in RACFs are identified upon arrival to ED within EDIS^®^ and recorded as arriving by ambulance from a nursing home. Data extraction will occur retrospectively from state-based and MNHHS databases. An anonymous unique identifier (linkage ID) will be assigned to all cases by the Queensland Health Statistical Service Branch (SSB), enabling linkage of data from all sources (Table 1). These data provided to the researchers will not contain any key patient identifying features such as Unit Record Number (URN), name, address or Date of Birth (DOB). However, data such as age, postcode, and health facility will be included in the collection.

**Table 1 Tab1:** Data sources, date ranges and data descriptions for the OPEN AOS evaluation study

Data Source	Time Period	Data Description
RADAR Registry	1 Jul 2022 to 30 Jun 2023	OPEN AOS activity plus outcome data including: • outcomes of intervention • time stamps • clinician delegation Patient demographics for matching variables
Emergency Department Information System (EDIS^®^)	1 Jul 2022 to 28 Jul 2023	ED presentations of cohort members at one of the participating hospitals. • outcomes of intervention • time stamps Patient demographics and RACF address (presentation postcode and suburb) for matching variables
Metro North Health Funding and Data Insights	1 Jul 22 to 28 Jul 2023	Costs of initial ED presentations and subsequent re-presentations within 48 h and 28 days Patient unit record number for matching variables
Queensland Hospital Admitted Patient Data Collection	1 Jul 2020 to 30 Jun 2023	Patient co-morbidities identified during any hospital admission (using ICD-10-AM codes and ICD-10-AM code chapters), during the 24-month period preceding their presentations to the ED Patient demographics for matching variables
Death Registrations from the Registry of Births, Deaths and Marriages Queensland Cause of Death Unit Record File from the Australian Coordinating Registry	1 Jul 2022 to 02 Jul 2023	Death within 48 h of discharge from either emergency department presentation or OPEN AOS intervention Patient demographics for matching variables
RiskMan Queensland Health’s system for recording and managing clinical incidents, workplace events, consumer feedback, and risk	1 Jul 2022 to 02 Jul 2023	Patient Clinical Incident data within 48 h of discharge from the ED Patient demographics for matching variables

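### Death and incident windows open only at discharge, so events during care go uncounted, and controls admitted from the ED are largely not at risk of re-presentation at 48 h

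*Protocol article*

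**What the plan says.** Three safety-related secondary outcomes of Component 1 are tied to discharge, each in a different way.

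- **Death.** Table 1 (Data collection and linkage) takes deaths within 48 h "of discharge from either emergency department presentation or OPEN AOS intervention". Both services are named.
- **Clinical incidents.** Study design defines these as "clinical incidents that are reported by MNHHS staff that occur within 48 h of discharge". The RiskMan row of Table 1 describes the data as "Patient Clinical Incident data within 48 h of discharge from the ED". OPEN AOS is not named there.
- **Re-presentation.** Study design lists "ED re-presentation for any cause within 48 h and 28 days of discharge" and does not say from what the patient is discharged.

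The primary outcome and the length of care episode, by contrast, both start at first contact with QAS. The inclusion and exclusion criteria do not remove controls who are admitted from the ED. Data analysis (Component 1) plans logistic regression for re-presentation and mortality and states no handling of admission. It mentions death only as a reason for censoring in the time outcomes.

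**The concern.** Aim 1 includes a comparison of safety. A window that opens at discharge opens at a time that depends on the model of care, and this has three effects.

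1. Whatever happens between QAS contact and discharge is outside every safety outcome, and the interval left out is probably longer for ED patients. The Abstract argues for the model partly from iatrogenic risk to older adults attending EDs, yet an incident during the ED stay would not be counted.
2. If discharge means leaving the ED, a control who leaves by admission is an inpatient and is largely not at risk of an ED re-presentation in the next 48 h. An OPEN AOS patient who stays in the facility is at risk throughout.
3. Incidents are those reported by MNHHS staff. Admitted controls remain under those staff. Residents who stay in the facility mostly do not: Setting gives 85 of 87 facilities as non-government. Incidents are therefore likely to be captured less completely for OPEN AOS.

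Re-presentation also feeds Component 2, so a distortion there carries into the incremental cost per patient.

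**Working it through.** **Plan's own figure.** For d = 0.2, two-sided alpha 5%, 90% power and a 1:3 ratio, the intervention group needs (1.960 + 1.282)² × (1 + 1/3) / 0.2² = 10.507 × 1.333 / 0.04 = 350.2. That rounds up to 351, with 1053 controls. Power by the noncentral t distribution is 0.900. The figure reproduces and concerns the primary outcome only. The article gives no figure for the safety outcomes.

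**Which discharge?** Table 1 dates:
- ED data end 28 July 2023 = 30 June + 28 days.
- Death and RiskMan data end 2 July 2023 = 30 June + 48 h.
- Admitted-patient data end 30 June 2023 and are described as a source of earlier comorbidities.

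None leaves room for an inpatient stay after a late-June presentation. ED departure is the likely origin for re-presentation, but this is an inference.

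**Re-presentation at 48 h.** Let r be the true risk while at risk, equal in both groups, and a the share of controls admitted. Assume that all admitted controls are still inpatients at 48 h and that no OPEN AOS patient is admitted. Observed control risk is r(1 − a), so the spurious risk ratio is 1/(1 − a), whatever r is. With r = 5% (assumed) and 351 v 1053 patients in an unadjusted comparison of proportions:

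| a (assumed) | Control risk | Risk ratio, OPEN AOS/control | Chance of a false difference |
|---|---|---|---|
| 20% | 4.0% | 1.25 | about 14% |
| 40% | 3.0% | 1.67 | about 43% |
| 60% | 2.0% | 2.50 | about 80% |

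**Re-presentation at 28 days.** Let R be the true 28-day risk, with constant hazard h = −ln(1 − R)/28, and L the inpatient stay in days. Control risk is (1 − a)R + a[1 − exp(−h(28 − L))]. Assumed ranges: R 15-25%, a 20-60%, L 3-10 days.
- Low end, R = 15%, a = 20%, L = 3: control risk 14.7%, ratio 1.02.
- High end, R = 15%, a = 60%, L = 10: control risk 11.95%, ratio 1.26.

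**Deaths during care.** Let m be 48 h mortality and e the episode length in hours, with hazard −ln(1 − m)/48. Deaths left out = n[1 − exp(−hazard × e)]. All inputs are assumed.
- m = 1%, e = 3 h (OPEN AOS) and 6 h (ED): 0.22 of 351 and 1.32 of 1053.
- m = 4%, e = 4 h and 16 h: 1.19 of 351 and 14.2 of 1053.

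**Incidents.** No arithmetic applies. The death row names both services, the RiskMan row only the ED, and the outcome definition neither. Read literally, the RiskMan row gives OPEN AOS discharges no window.

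**The case against.** The best defence is that the article leaves detailed outcome definitions to Additional file 2, which is not shown and may say what discharge means for an admitted patient. That stands as a reason to check the file first. It does not dispose of the point, because any definition there must still agree with the rows and dates in Table 1. It is also fair that the RiskMan row may be loose wording: the extract runs continuously over the study year and the outcome definition is not limited to ED patients. Aligning one row may settle that part.

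A reader might go further than the text allows in three ways.

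- *Admitted controls cannot re-present.* This is close to true at 48 h only. Over 28 days they can re-present after leaving hospital, and the distortion is much smaller.
- *Deaths of admitted controls are lost.* They are not. An inpatient death within 48 h of leaving the ED is captured through death registrations, and harm early in an admission falls inside an ED-departure window. Only deaths before discharge fall outside, and only if a death in the ED is not itself coded as a discharge, which the article does not say. Patients given emergency status are excluded, so these deaths should be few.
- *The safety comparison is invalid.* The article does not support that. The likely biases run in different directions: re-presentation against OPEN AOS, incident reporting in its favour, and omitted deaths during care probably in favour of the control group.

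The 48 h ratios also rest wholly on assumed admission shares. They fall if some admitted controls go home within 48 h, or if some OPEN AOS patients are transported and admitted.

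**Conclusion.** The point holds as one of definition and likely bias in secondary outcomes. Three parts follow from the text without any assumed figure: the death and incident windows open at discharge, the RiskMan row omits OPEN AOS, and admitted controls are neither excluded nor handled in the re-presentation analysis. That re-presentation is counted from ED departure is inferred from the extract dates.

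On that reading, and with equal true risks, the spurious 48 h risk ratio is about 1.25-2.5 for 20-60% admitted, an upper bound for each share. At 28 days it is about 1.02-1.26. The size of the incident-reporting difference cannot be derived from the article. Matching and the listed covariates do not remove a difference in who is at risk. This should be fixed before the extracts are final. The primary outcome, which already runs from QAS contact, is not touched.

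**What to change.** 1. **Death and incidents.** Count both from first QAS contact over the same fixed window in each group, and report events during care and after care separately. A 48 h window needs no new death or RiskMan dates: the last eligible contact is no later than 20:00 on 30 June 2023, so the window closes by 20:00 on 2 July.
2. **RiskMan row.** Align it with the outcome definition so that OPEN AOS episodes are covered. State as a limitation that reporting by MNHHS staff probably captures fewer incidents among residents who stay in the facility.
3. **Re-presentation.** Define discharge for admitted patients. Use first QAS contact as the common origin, with a composite of unplanned acute hospital use after the index episode, or treat index admission and death explicitly as competing events. In either case say how an admission straight from the index ED visit enters, and whether transport of an OPEN AOS patient to the ED counts as an event. Starting the clock at return to the facility is not a good substitute: that start also depends on treatment and would need ED data beyond 28 July 2023.
4. **Sensitivity analysis.** Repeat the comparison with controls limited to those discharged home from the ED. It selects on something that happens after the start of care, so it should not be the main analysis.

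Cost: redefinition, one table row, and extension of the admitted-patient extract from 30 June to 28 July 2023. If death is a competing event, the death extract moves from 2 July to the same date. The data are retrospective and already to be linked, so this is modest.

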### Data analysis

For our analysis, the comparison of interest is between the intervention and control groups. Re-presentations by patients in either group are not considered as independent events and will be excluded from analyses, however the number of re-presentations during the study period will be noted for the OPEN AOS group. Categorical data will be presented as frequency and percentages, while continuous data will be reported as mean with standard deviation or median with interquartile ranges, depending on the distribution of the data. Categorical data will be analysed using the Pearson Chi-squared test or Fisher’s exact test, and continuous variables using the Student t-test or Mann-Whitney U test. Time to treating emergency clinician and time to discharge from the episode of care will be examined using a generalised linear model or parametric regression model if events are censored e.g., death of a patient. ED re-presentation and mortality will be examined using logistic regression if there are sufficient events. All regression models will be multivariable with fixed effects for triage score, weekend presentation, season, and ambulance referral time. The inclusion of Charlson Comorbidity Index [52] in regression analyses will depend on the extent of missing data. Component 1 will be reported in accordance with the Enhancing the QUAlity and Transparency Of health Research (EQUATOR) guidelines for reporting non-randomised studies [53].

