## Intervention: the OPEN AOS model

The OPEN AOS model provides emergency substitution care to older adults residing in RACFs located within the MNHHS catchment area. Nurse-led and physician supported, OPEN AOS commenced in January 2022 and became fully operational by June 2022. The service is based in office space adjacent to a MNHHS hospital and operates 12 h per day between the hours of 08:00–20:00, Monday to Sunday. The service aims to (i) decrease the time to treating emergency clinician and (ii) reduce the number of avoidable ambulance transports to ED for older adults living in RACFs. The OPEN AOS model is staffed by 3.0 full-time equivalent (FTE) Nurse Practitioners^1^ (NP); 1.0 FTE NP candidates (NPC)^2^; and 1.8 FTE RNs^3^ [40, 41]. The model is supported by 1.4 FTE Senior Medical Officers (SMO)^4^ [42, 43] and 0.8 FTE Senior Pharmacists 5 [44]. The service is funded by MNHHS. Detailed descriptions of the responsibilities of the OPEN AOS clinical roles are provided in Additional file 1.

Patients of OPEN AOS are older adults residing in RACFs experiencing acute illnesses or injuries. OPEN AOS clinicians provide emergency substitution care via telehealth or in person. Referrals originate from the ambulance service (either from paramedics attending the patient at the RACF or following secondary telephone triage by experienced ambulance service clinicians), General Practitioners (GPs), RACF staff and other local teams providing specialist sub-acute RACF consulting services. Each referral is reviewed by an OPEN AOS clinician who triages the case and determines suitability for OPEN AOS care. Patients not meeting eligibility criteria for the OPEN AOS remain in the care of ambulance services for secondary triage and receive standard clinical review, consideration of referral pathways and standard ambulance attendance.

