### Samples

In the 12-month study period from 1 July 2022 to 30 June 2023, approximately 7600 ED presentations from RACFs arrived by ambulance to district’s ED sites. During that same period, 735 patients were treated by OPEN AOS during their operational hours (08:00–20:00) Monday to Sunday. Patients treated in the Intervention group will be matched with up to three randomly selected control group patients without replacement with matching on age (+/- 5 years), and exact matching on sex and diagnostic classification section (or chapter if diagnoses are uncommon) as per the International Classification of Diseases, 10th Revision Australian Modification (ICD-10-AM) using the ‘R’ package Matching: Multivariate and Propensity Score Matching with Balance Optimization [50]. Groups sizes of 351 for the intervention group and 1053 for the control group will achieve 90% power to reject the null hypothesis of no effect on the time to be seen by treating clinician when there is a Cohen’s d small effect size of 0.2 using a two-sided, two-sample test assuming equal variance and an alpha of 5% [51].

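### Clinical incidents are the only between-group Component 1 outcome for which the analysis section names no adjusted model, even when events are sufficient (minor)

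*Protocol article*

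**What the plan says.** The Study design section of the protocol article asks whether outcomes differ between OPEN AOS and standard care, and lists six Component 1 outcomes. One of them, ambulance transport, is "defined as the proportion of OPEN AOS patients requiring transport to ED for definitive care", so it has no control arm. The other five are compared between groups. The last is clinical incidents, defined as "clinical incidents that are reported by MNHHS staff that occur within 48 h of discharge".

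The Component 1 Data analysis section sets a default: "Categorical data will be analysed using the Pearson Chi-squared test" or Fisher's exact test. It then names models outcome by outcome:

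- For the two time outcomes: "Time to treating emergency clinician and time to discharge from the episode of care will be examined using a generalised linear model". Where there is censoring, a parametric regression takes its place.
- For two of the binary outcomes: "ED re-presentation and mortality will be examined using logistic regression if there are sufficient events".

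On covariates, the section adds one rule that applies throughout: "All regression models will be multivariable with fixed effects for triage score, weekend presentation, season, and ambulance referral time".

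The section does not mention clinical incidents. The Samples section matches on age within 5 years, sex and ICD-10-AM diagnostic section or chapter, not on triage score. Under the description of the intervention, an OPEN AOS clinician reviews each referral, "triages the case and determines suitability for OPEN AOS care".

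**The concern.** Safety is part of the first study aim, and incidents and death within 48 h are its two direct harm outcomes. Deaths get the adjusted model if there are enough of them. Incidents are given none, however many there are. A chi-squared or Fisher test cannot carry triage score, which the plan itself treats as a standard covariate.

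The service selects its patients at triage. Excluding emergency-status cases and matching on diagnosis narrow an acuity difference but need not remove it. If triage mix differs, a crude test can hide an excess of incidents or show a false one. The harm comparison would then rest on a weaker method than the plan already has to hand.

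**Working it through.** **1. Map each outcome to its stated analysis.**

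| Component 1 outcome | Compared between groups? | Adjusted model named? |
|---|---|---|
| Time to treating clinician | yes | yes |
| Length of care episode | yes | yes |
| Ambulance transport to ED | no (OPEN AOS only) | no |
| ED re-presentation, 48 h and 28 days | yes | yes, if events suffice |
| Death within 48 h | yes | yes, if events suffice |
| Clinical incidents within 48 h | yes | no |

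Incidents are the only between-group outcome without a named model.

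**2. The plan's own figure.** With 351 v 1053 patients and d = 0.2, the standardised difference is 0.2 / √(1/351 + 1/1053) = 3.245, and power is Φ(3.245 − 1.960) = 0.90. The stated 90% reproduces, but it concerns the primary outcome and says nothing about incidents.

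**3. Size of a possible distortion.** All inputs here are assumptions: a 3% incident rate in controls, a two-level triage class with incident odds three times as high in the upper class, and 50% of controls v 35% of OPEN AOS patients in that class.

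- Class risks that average 3% in controls with an odds ratio of 3: 1.534% and 4.466%.
- OPEN AOS risk with no true effect: 0.65 × 1.534% + 0.35 × 4.466% = 2.560%.
- Crude odds ratio: (0.02560/0.97440) / (0.03/0.97) = 0.02627/0.03093 = 0.85.
- With the shares reversed, about 1.18. A true odds ratio of 2 appears as about 1.7, or 2.3 reversed.
- With odds doubled rather than tripled, and 40% or 35% v 50%, a true odds ratio of 1 appears as 0.89 to 0.94.

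**4. When adjustment pays.** Simulated data sets of 351 + 1053 and 735 + 2205 patients used the tripled-odds assumption, control rates of 0.5% to 5% and a true odds ratio of 1 or 2. They compared group alone with group plus triage, both by penalised logistic regression. RMSE is the root mean squared error of the log odds ratio.

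| Events | RMSE change with adjustment | Coverage of crude 95% interval |
|---|---|---|
| 7–20 | +1% to −5% | 94–98% |
| 27–39 | −4% to −10% | 92–95% |
| 41–62 | −6% to −13% | 90–94% |
| 67–116 | −11% to −21% | 88–92% |
| 142–191 | −21% to −30% | 82–89% |

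Adjusted coverage was 94% to 97% throughout. With no confounding, adjustment raised RMSE by 0.1% to 1.2%. With doubled odds, RMSE fell by 0% to 11%.

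The plan's full covariate set (7 slopes) was also compared with the chi-squared test under tripled odds. With no true effect and 68 to 153 incidents, the false-positive rate was 3.5% to 5.0% adjusted v 5.4% to 13.3% crude. With a true odds ratio of 1.5, OPEN AOS patients less acute and 94 incidents, power was 42.5% v 19.0%. Those 94 incidents correspond to a 3% control rate in 735 + 2205 patients: 2205 × 3.00% + 735 × 3.78% = 66 + 28.

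**5. What the counts mean as rates.** Thirty events are 30/1404 = 2.1% of 351 + 1053 patients, or 30/2940 = 1.0% of 735 + 2205. At the common rule of 10 events per parameter, 7 slopes need 70 events: 5.0% or 2.4%. The figure of 735 is all patients treated in operational hours and is not stated to be net of exclusions, so 2940 is an upper limit.

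**The case against.** The strongest objection is that this rests on silence in a condensed article. The analysis section never says that incidents will not be modelled. An unseen analysis plan may name a model, and Additional file 2 holds the detailed outcome definitions. That stands in part: a reader might infer that the plan commits incidents to a crude test whatever the count, but this is drawn from a list and is not stated. What remains is that the article does not defer the choice. It names the modelled outcomes and gives one default for the rest, so following it gives incidents the crude test.

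A reader might also infer that the plan requires triage adjustment for every other between-group outcome. It does not. Only the two time outcomes have it without condition; re-presentation and mortality have it if events suffice. If incidents are few, they are treated as deaths would be.

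Rare events are plausible. Incidents must be reported by health-service staff within 48 h, and 85 of the 87 facilities are non-government. With 7 to 20 events the gain is negligible. The larger contrasts above need 68 or more incidents and the stronger confounding assumption.

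Capture may be the more basic problem. Table 1 describes the incident data as following discharge from the ED, whereas its death row covers ED and OPEN AOS discharges alike. Triage adjustment cannot repair an outcome recorded differently in the two groups. It also assumes that triage score is comparable across groups, as the plan itself does.

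Finally, the Limitations section already concedes selection bias and baseline differences. That tempers interpretation but does not justify leaving out a covariate that is available.

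**Conclusion.** The point holds as a minor inconsistency. Clinical incidents are the one between-group Component 1 outcome without a named adjusted model even if events are sufficient, although triage score is in all the plan's regressions and is not matched on.

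Its size is conditional. It depends on a triage imbalance that the documents do not quantify and on the incident count: small below about 20 to 30 events, material above that if triage is both imbalanced and prognostic. Every odds ratio, RMSE, coverage, error-rate and power figure for incidents rests on assumed rates, a two-level triage class and one binary outcome per patient.

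A reader might go further and infer that the safety comparison is biased towards hiding harm. The documents do not support this: they establish neither the size nor the direction of any bias. Nor do they show a fault in the mortality analysis, where the event condition is sensible.

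**What to change.** In the Component 1 Data analysis section, add clinical incidents to the outcomes that get logistic regression, under the same condition of sufficient events and with the covariates already stated. Say that incidents are coded per patient as any incident v none. If incidents are instead to be analysed as counts or severity classes, the model should be named to suit.

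The cost is a few words. Triage score is already planned for every regression, so no new data are needed. The statistical price is marginally wider intervals: the standard deviation of the log odds ratio rose by about 0% to 3% in the simulations.

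A sparse-data fallback, such as Firth-penalised logistic regression with group and triage score, is optional. No change to the mortality analysis is needed. The amendment does not address incident capture in OPEN AOS patients, unmeasured confounding or low power, which should be considered separately when the result is interpreted.

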## Setting

The study is set in the Metro North Hospital and Health Service (MNHHS) district in south-east Queensland, Australia [35]. In 2024, the MNHHS region had 87 RACFs (85 non-government) with 9417 RACF beds. The district is serviced by five public hospitals; four are classified as large or very large and one is classified as small. The EDs within each of the five hospitals vary in their level of service capability and capacity [36, 37].

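### Component 1 builds a variable-ratio matched sample, but its stated tests and models carry no matched-set weight or term, no matching variables and no ED catchment, so the estimate may be biased and its standard error misstated

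*Protocol article*

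**What the plan says.** **Design.** In the Samples section, intervention patients "will be matched with up to three randomly selected control group patients without replacement with matching on age" (within 5 years), with exact matching on sex and on ICD-10-AM section. Chapter replaces section where a diagnosis is uncommon. Three is a ceiling, so the ratio can vary from patient to patient.

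**Power.** "Groups sizes of 351 for the intervention group and 1053 for the control group will achieve 90% power" for a "small effect size of 0.2", "using a two-sided, two-sample test assuming equal variance and an alpha of 5"%. The basis is two independent groups at exactly 1:3.

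**Analysis.** The Component 1 Data analysis section analyses categorical data with chi-squared or Fisher tests and "continuous variables using the Student t-test or Mann-Whitney U test". Time to clinician and time to discharge go to a generalised linear or parametric regression model. Re-presentation and mortality go to logistic regression if events suffice. For all of these, "All regression models will be multivariable with fixed effects for triage score, weekend presentation, season, and ambulance referral time". The Charlson index is added if missing data allow.

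**Location.** The Setting section says "The EDs within each of the five hospitals vary in their level of service capability and capacity". The EDIS row of Table 1 lists "Patient demographics and RACF address (presentation postcode and suburb) for matching variables", but Samples does not name location as a matching variable.

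**The concern.** With a constant ratio, every stratum of age, sex and diagnosis has the same share in both groups, so a simple pooled comparison is balanced on the matching variables. With a varying ratio, that balance holds only if each control is weighted by one over the number matched in its set, or if the set or the matching variables enter the model. The plan provides none of these.

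Scarcity of controls is likely to follow diagnosis, since diagnosis is matched exactly and the plan itself expects uncommon ones. Diagnosis may then confound the comparison again. Age, matched only to within 5 years, also keeps some residual difference.

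Two further features are absent. Time to clinician in the control group depends on which of five differing EDs receives the patient, yet no catchment term is listed. Patients also share facilities, yet no facility term or clustered variance is listed.

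At stake are the primary outcome and the re-presentation figures that Component 2 takes from Component 1.

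**Working it through.** **1. The plan's own figure.** With 351 and 1053 patients and SD 1, the standard error is √(1/351 + 1/1053) = 0.0616. Then 0.2/0.0616 − 1.96 = 1.285, which gives power of 0.90. The figure reproduces and is not disputed. It assumes independence and a full 1:3.

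**2. Imbalance from a varying ratio.** Let a share *s* of intervention patients lie in scarce strata with *k* controls each, and let the rest have three.

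- Control share of scarce strata = *s·k* / (*s·k* + 3(1 − *s*))
- Bias = (*s* − control share) × *g*, where *g* is the outcome difference between strata in SD

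The article gives none of *s*, *k* or *g*, so these are assumptions:

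| *s* | *k* | Control share | *g* | Bias (SD) |
|---|---|---|---|---|
| 0.20 | 2 | 0.4/2.8 = 0.143 | 0.3 | 0.057 × 0.3 = 0.017 |
| 0.30 | 1 | 0.3/2.4 = 0.125 | 0.5 | 0.175 × 0.5 = 0.0875 |
| 0.30 | 1 | 0.125 | 0.8 | 0.175 × 0.8 = 0.14 |
| any | 3 | equals *s* | any | 0 |

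The middle case is 0.0875/0.2 = 44% of the planning effect. The sign depends on whether the scarce strata wait longer or shorter.

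**3. Simulation check.** This used 351 intervention patients, no true effect, 1500 runs per setting and a binary matching factor left out of the model.

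- Fixed 1:3: bias about 0; type I error 0.043 (factor effect 0.5 SD) and 0.027 (1.0 SD).
- Varying ratio, with 40% of patients having one or two controls: bias 0.03 SD and type I error 0.061 (factor effect 0.2 SD); bias 0.08 SD and type I error 0.218 (0.5 SD).
- Varying ratio with the matching factor added to the model: bias about 0; type I error 0.045 to 0.047.

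**4. Standard error, matched sets.** At a full 1:3 with within-set correlation ρ, the ratio of true to independent-group standard error is √(1 − ρ). It is 0.975 at ρ = 0.05 and 0.837 at ρ = 0.30, so the planned standard error is too wide.

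**5. Standard error, facilities.** With 87 RACFs and assumed ICCs of 0.02, 0.05 and 0.10, ignoring facilities gives type I error of 0.053 to 0.057 when both groups spread evenly. When OPEN AOS use differs strongly between facilities, it gives 0.049, 0.081 and 0.118. The article states neither the ICC nor the pattern of use.

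**6. Catchment.** Suppose ED means of −0.4, −0.2, 0, 0.2 and 0.4 SD and controls spread 20% to each ED. The bias is the sum of ED mean × (intervention share − 0.2). Shares of 30/25/20/15/10 in the same order as the ED means give 0.10 in size; 50/20/10/10/10 gives 0.18. Other orders shrink or reverse this. With 30/25/20/15/10 set against means of 0.4, −0.4, −0.2, 0 and 0.2, the sum is 0.04 − 0.02 + 0 − 0 − 0.02 = 0. The assumptions therefore span −0.18 to +0.18 and include zero, so no size can be claimed.

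**The case against.** **The bias is conditional.** Samples gives about 7600 ambulance presentations from RACFs against 735 OPEN AOS patients, roughly 10 to 1, and falling back to ICD chapter eases scarcity. If nearly all patients obtain three controls, the bias is negligible. This stands, and it is why the size is illustrative only. However, 7600 counts presentations before the limits on hours, triage status, residency and first presentation. A full 1:3 for 735 patients would need 3 × 735 = 2205 controls, although exclusions reduce the 735 as well.

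**Planned adjustment may absorb part of it.** Triage score may carry some of the link from diagnosis to waiting time. This is fair: the assumed *g* is not net of triage. It is no substitute for the matching variables, though. Triage is itself unmatched, so conditioning on it does not preserve the matched balance.

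**The unpaired tests are not the main analysis.** The primary outcome, episode length, re-presentation and mortality all go to regression. This stands, so the weight of the point falls on the model specification.

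**A fuller plan may hold the detail.** Weights and variance estimators are often left to one. But the article specifies the tests and a covariate list for all regression models, and that stated analysis does not fit the stated design.

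**Location may already be matched.** Table 1 can be read that way, or as referring to record linkage. Either way, it and Samples need to be reconciled.

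A reader might infer that the estimate and its error bars are certainly wrong, that catchment adds 0.10 to 0.18 SD of bias, or that clustering inflates the 5% error rate to about 11 or 12%. The documents support none of these. Each needs an achieved ratio, ED shares and means, or an ICC with uneven uptake, and none of these is given.

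**Conclusion.** The point holds in conditional form and should be fixed before analysis. The stated tests and models do not carry the variable-ratio matching, the matching variables or the ED catchment.

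- **Bias:** if the number of controls found depends on diagnosis, about 0.02 to 0.14 SD against a planning effect of 0.2. This assumes 20 to 30% of patients with one or two controls and strata 0.3 to 0.8 SD apart. It is about zero at a full 1:3.
- **Standard errors:** possibly off in either direction. Ignoring matched sets is conservative at a full 1:3; ignoring facilities is anti-conservative only if OPEN AOS use is uneven between them and the ICC is not negligible.
- **Catchment:** a plausible confounder of time to clinician, because the article says the EDs differ, but unquantified.

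The sample-size arithmetic is correct. Dependence within patients is dealt with, since repeat presentations are excluded and matching is without replacement.

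**What to change.** In the Component 1 outcome models:

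1. Weight each control by 1/k, where k is the number of controls in its matched set, or stratify by set.
2. Add age (continuous), sex and diagnosis stratum as covariates.
3. Use standard errors clustered on matched set.
4. Treat the unpaired tests as descriptive.
5. Add hospital catchment, derived from RACF postcode or suburb, as a fixed effect. Reconcile Samples with Table 1 on whether RACF location is a matching variable.
6. Where an RACF identifier or postcode is available for both groups, report RACF-clustered standard errors as a sensitivity analysis.

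**Cost.** Items 1 to 4 need wording, a few lines of code and a few degrees of freedom. Weighting loses a little precision. With 30% of sets at k = 1 and 70% at k = 3, the variance factor goes from 1 + 1/2.4 = 1.417 to 1 + 0.3 + 0.7/3 = 1.533, so the standard error widens by √(1.533/1.417) = 1.04, about 4%.

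Items 5 and 6 depend on the data. Table 1 lists postcode and suburb only in the EDIS row, and the RADAR row shows no RACF address. The section text promises postcode and health facility but no clear RACF identifier. Availability for the OPEN AOS group should be confirmed first.
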